#### Recreational activity.

Recreational physical activity will be assessed at each timepoint using items from the How Areas in Brisbane Influence Health and Activity (HABITAT) study [41] which will be modified to reflect recreational activity over the previous month. Participants rate how often they did 15 activities (e.g. running or jogging, team sports, water activities) on a 5-point scale (never, once a month, once every 2 weeks, once a week, more than once a week). Participants will also report the number of hours they watch television or use an electronic device (computer, tablet, smartphone, video games) in their free time (1) on typical a weekday and (2) on typical a weekend day.

#### Dietary intake

Dietary intake will be assessed at each timepoint using the online Dietary Questionnaire for Epidemiological Studies (DQES v3.2; Cancer Council Victoria) [42], which will be modified to reflect diet over the previous month. The DQES v3.2 is an online self-administered questionnaire that estimates nutritional intake (grams of foods, macro nutrients and micronutrients) based on 144 foods and beverages using nutritional information from the NUTTAB 2010 [43] and AUSNUT 2007 [44]. The DQES has been demonstrated to have good reproducibility and has good agreement with weighed food records [45, 46].

#### Psychological wellbeing

Quality of life will be assessed at each timepoint using the World Health Organization Quality of Life assessment 26-item version (WHOQOL-BREF) [47]. WHOQOL-BREF is a self-report questionnaire which measures four broad domains: physical health, psychological health, social relationships and environment. The WHOQOL-BREF has good discriminant validity, content validity, test-retest reliability and internal consistency [47–49]. The online version of the questionnaire is a valid and reliable alternative to the original paper-based version of the questionnaire [50].

Symptoms of depression, anxiety and stress will be assessed at each timepoint using the 21-item short-form Depression Anxiety Stress Scale (DASS-21) [51]. Participants rate the extent to which they agree with 21 statements such as “I found it hard to wind down” on a 5-point scale from 1 “Did not apply to me at all” to 5 “Applied to me very much, or most of the time”. The DASS-21 has good convergent and discriminant validity when compared with other validated depression and anxiety measures, adequate construct validity, and high reliability [51–53].

#### Weight perception and management

At baseline, participants will report whether they consider themselves to be an acceptable weight, underweight or overweight and whether they have been weight stable (within 5% of body weight) in the past 3 months [54]. At each timepoint, participants will report whether they have used a range of weight control practices in the past month (adapted from the Behavioral Risk Factor Surveillance System [55]) and whether they currently use any medication from a list of six broad categories that can be associated with weight change [56, 57].

#### Work/holiday status

At baseline, participants will report their occupation (open-ended response), whether they work shift work that includes some night shifts, and whether they regularly work on weekends. At each time point, participants will report their average hours of work outside the home (none, less than 15 h per week, 15 to 30 h per week, fulltime 36h hours per week), whether (and on what days) they have been on holidays or had annual leave since the last assessment (in the previous month at baseline), and whether (and on what days) they were away from home during that time.

#### Family environment

A range of family environment measures will be completed at baseline. Parenting style will be measured using the parenting warmth and parenting consistency scales from the Longitudinal Study of Australian Children [58]. Participants will report how they encourage their child’s physical activity on a 4-item scale adapted from adapted from ISCOLE Neighborhood and Home Environment Questionnaire [59] and describe how meals take place on the “Structure of Family Meals” subscale of the Meals in Our Household Questionnaire [60]. Participants will also report whether a TV, computer or video game system (non-hand held; PlayStation, Xbox, etc.) are in their bedroom and their child’s bedroom (adapted from ISCOLE [59]).

#### Baseline covariates

At baseline, participants will report their date of birth, sex, country of birth, marital status (never married, widowed, divorced, separated but not divorced, married or de facto), number of adults and number of children at home. Socioeconomic status measures include highest education level (below year 10, year 10, year 11, year 12 or equivalent, certificate III/IV, advanced diploma/diploma, bachelor degree, postgraduate or higher degree), combined gross household income (<$50,000, $50,000–$99,999, $100,000–$199,999, ≥$200,000), number of motorised vehicles in the household, and type of television/streaming service. Participants will report their smoking status and whether they have any of ten listed chronic conditions (adapted from the Australian National Health Survey [1]). Participants will also report their sleep chronotype (single item from both the Horne-Östberg Morningness-Eveningness-Questionnaire [61]) and complete an 8-item scale assessing their tendency towards routine [62].

### Power calculation

Due to the complex nature of the multilevel model addressing Aim 1, current sample size software is unable to estimate the required sample size. We have therefore calculated the required sample size for a multivariable linear regression model, using conservative estimates, with added adjustments for clustering within families. For the initial estimate, a sample size of 226 achieves 90% power to detect an r^2^ of 0.10 attributed to 10 independent variables when the significance level (alpha) is 0.025. In addition, data are clustered within families, with an expected average cluster size of 1.5, and an ICC of 0.7. This equates to a design effect of 1.35, bringing the required total to 305 subjects. Allowing for 20% withdrawals/loss to follow up, the final sample size is 371. These estimates are approximate, but suggest that the anticipated sample size of 375 will provide sufficient power.

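### Protocol article, Power calculation: the final sample size of 371 does not follow from 305 subjects and 20% loss, which give 382; the planned 375 is 7 below that, with little effect on power (minor)

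*Protocol article*

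**What the plan says.** The Power calculation section explains that the multilevel model for Aim 1 is too complex for available sample size software. It therefore uses a multivariable linear regression as a stand-in and adjusts the result in steps.

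- Base size: "a sample size of 226 achieves 90% power to detect an r^2^ of 0.10 attributed to 10 independent variables". Alpha for this test is set at 0.025.
- Clustering within families: "with an expected average cluster size of 1.5, and an ICC of 0.7".
- Result of that adjustment: "This equates to a design effect of 1.35, bringing the required total to 305 subjects".
- Attrition: "Allowing for 20% withdrawals/loss to follow up, the final sample size is 371".

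The section then describes the estimates as approximate and says that they "suggest that the anticipated sample size of 375 will provide sufficient power". The same 375 is the recruitment target in the Methods part of the Abstract and in Participants and procedure.

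**The concern.** The last step divides one printed number by another printed number, and the answer printed is not the quotient. The section gives no second loss rate and no different inflation rule that would produce 371.

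The step matters because the adequacy of the recruitment target rests on it. As printed, 371 is less than 375 and the target appears to be met with a little to spare. With the division done correctly, 375 is less than 382 and the target is slightly missed on the plan's own terms. What is at stake is the accuracy of a published sample size justification, and a small overstatement of what 375 delivers.

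**Working it through.** **Inputs**, all from the Power calculation section: base n = 226 for 90% power, R² = 0.10, 10 predictors, alpha = 0.025; mean cluster size m = 1.5; ICC = 0.7; loss d = 20%; stated final size 371; anticipated size 375.

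**Step 1: base size.** The test is the overall F test of R² with 10 and n − 11 degrees of freedom and f² = 0.10/0.90. The document does not say whether predictors were treated as fixed or random, so both were computed.

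| n | Power, random predictors | Power, fixed predictors |
|---|---|---|
| 225 | 89.96% | 90.7% |
| 226 | 90.1% | 90.8% |

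With random predictors, 226 is exactly the smallest n that reaches 90%. With fixed predictors 222 would be enough. The plan's 226 is reproduced.

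**Step 2: clustering.** Design effect = 1 + (m − 1) × ICC = 1 + 0.5 × 0.7 = 1.35, and 226 × 1.35 = 305.1. The plan's 1.35 and 305 are reproduced.

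**Step 3: loss to follow-up.** To retain 305 after losing a fraction d, enrol 305/(1 − d).

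- Correct inflation: 305/0.80 = 381.25, rounded up to 382.
- Common shortcut: 305 × 1.2 = 366.
- Loss applied before clustering: 226/0.80 × 1.35 = 381.4, and 226 × 1.2 × 1.35 = 366.1.
- Starting from 306 instead of 305: 306/0.80 = 382.5 (383), and 306 × 1.2 = 367.2 (368).

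None of these gives 371. Worked backwards from 305, 371 implies a loss of 1 − 305/371 = 17.8%. A base size of 220 would give 220 × 1.35/0.80 = 371.25, but the section prints 226 and 305, so this is only a possible origin.

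**Step 4: what the enrolled numbers deliver at 20% loss.**

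| Enrolled | Retained at 20% loss | Against 305 |
|---|---|---|
| 371 | 371 × 0.80 = 296.8 | 8 short |
| 375 | 375 × 0.80 = 300 | 5 short |
| 382 | 382 × 0.80 = 305.6 | met |

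The largest loss at which 375 still retains 305 is 1 − 305/375 = 18.7%.

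**Step 5: power at 375 with 20% loss.** Effective n = 300/1.35 = 222. At n = 222, power is 89.4% with random predictors and 90.1% with fixed predictors. Against n = 226 under the same convention, the reduction is 90.1 − 89.4 = 0.7 percentage points (random) or 90.8 − 90.1 = 0.7 points (fixed).

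**The case against.** The best defence is that nothing of substance changes. The section calls its estimates approximate, says its inputs are conservative, and uses the regression only as a stand-in for a multilevel model. The stated 371 is within 3% of 382 (11/371 = 2.96%). With fixed predictors, 375 at 20% loss still gives 90.1% power.

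Most of this stands, and it is why the point is minor. It does not rescue the figure. The caveat about approximation fits the choice of model; it does not cover a division of two printed numbers, and here the discrepancy reverses the comparison with 375.

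It is also fair to say that the text cannot show which number is wrong. The slip may lie in 371, in the 20%, or in a value further up. The figure 382 is correct given 305 and 20%; it is not proof that those two are the intended inputs.

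A reader might infer two stronger things that the document does not support:

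- **That the study is underpowered.** A shortfall of 5 retained subjects out of 305 costs less than one percentage point of power.
- **That the design effect is also wrong, because no family contributes 1.5 adults.** The 1.35 reproduces exactly from the stated mean cluster size and ICC, and using the mean is ordinary for a planning approximation. A different value would need the mix of one-adult and two-adult families, which the document does not give. Unweighted formulas for unequal clusters would not describe the multilevel model set out under Statistical analysis.

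**Conclusion.** Wrong as written, and minor. The step from 305 to 371 is not explained by the stated 20% loss; 305 and 20% lead to 382. On the plan's own figures, 375 is 7 below the number to enrol and leaves 300 analysable subjects instead of 305.

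Power at 375 is then about 89% to 90%, depending on whether predictors are treated as random or fixed. This takes the plan's R², number of predictors, alpha, design effect and loss rate as given. The claim that 375 is sufficient survives in substance, but the printed margin over the requirement does not.

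**What to change.** Reconcile the three figures 305, 20% and 371, checking the original calculation for a different base size or loss rate.

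- If 305 and 20% stand, replace 371 with 382 and keep 375. State that 375 yields 300 analysable subjects at 20% loss, with about 89% to 90% power, and that 305 is reached only if loss is at most 18.7%. Saying whether 226 came from the random-predictor or the fixed-predictor calculation would settle which end of that range applies.
- If another input was intended, print that input so that the chain leads to the stated result.

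The cost is a corrected sentence or two and a slightly less favourable stated figure. No extra recruitment and no change to the design or analysis is needed.

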### Statistical analysis

Longitudinal compositional data analysis methods will be used to assess activity and diet compositions. To account for the inherent co-dependency of compositional parts (proportions of time or macronutrients), compositions will be expressed as sets of isometric log ratios (ilrs) before their inclusion in statistical models [63, 64]. Aim 1 will use data from all participants. Aims 2 and 3 will use data only from parents/guardian of children enrolled in Life on Holidays and matched data from children in Life on Holidays.

#### Aim 1

Annual rhythms will be described graphically using Loess curves. Associations between change in weight (dependent variable) and changes in activity and diet compositions (independent variables) will be examined using multilevel modelling to adjust for non-independence of data, allowing for nesting of repeated measures within individuals and individuals within families. Diet and activity will be examined simultaneously to identify unique effects on weight. Covariates will include age, sex, socioeconomic status, and total energy intake.

#### Aim 2

Associations between change in children’s (dependant variables) and parents’ (independent variables) weight, activity, and diet compositions will be examined using a series of multilevel models to adjust for non-independence of data. Covariates will include parental and child age, sex, socioeconomic status, and child total energy intake.

#### Aim 3

Factor analysis will be used to derive factors from the baseline family environment items. The association between change in children’s body mass index z-score, and activity and diet compositions (dependant variables) and family environment (independent variable) will be examined using a series of multilevel models. Covariates will include parental and child age, sex, socioeconomic status, and total energy intake.

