### Measures

#### Body weight

Body weight will be measured using Fitbit Aria electronic weight scales (Fitbit Inc., San Francisco, CA, USA) [32, 33]. Participants will be encouraged to weigh themselves preferably daily but at least weekly, in the morning, whilst wearing minimal clothing, prior to meals and after voiding. Participants who do not wish to weigh in the morning will be asked to weigh at the same time on each occasion. Body weight data will be uploaded to participants’ Fitbit accounts and collected remotely via the Fitnesslink software. Height will be measured at baseline home visit using a stadiometer (Leicester Height Measure MKII). Measures will be conducted according to International Society for the Advancement of Kinanthropometry assessment procedures [34].

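### Aim 1 models change in adult weight with no starting body size among its named covariates, although height and weight are collected

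*Protocol article*

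**What the plan says.** The protocol article, Statistical analysis, Aim 1, sets out a change-on-change model: "Associations between change in weight (dependent variable) and changes in activity and diet compositions (independent variables) will be examined using multilevel modelling", "allowing for nesting of repeated measures within individuals and individuals within families". The adjustment set follows: "Covariates will include age, sex, socioeconomic status, and total energy intake".

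Height, baseline weight and BMI are not in that sentence. They are also not among the items in the Baseline covariates section, which covers self-reported characteristics. The Body weight section has adult height taken with a stadiometer at the baseline home visit and weight recorded on home scales, preferably daily and at least weekly. The material for baseline BMI is therefore collected, but the article states no analysis that uses adult height or BMI.

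**The concern.** Starting body size is an obvious candidate predictor of how much an adult's weight moves over a year. It may also relate to how much diet and activity move. If both hold, part of the association credited to diet or activity change belongs to starting BMI.

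The change-on-change form does not dispose of this. Taking changes removes stable effects of body size on the level of weight, but not effects on the size of the change. The article also does not say that the slopes will be split into within-person and between-person parts. Without that split, each slope draws partly on differences between people in how much they change, and that is where baseline BMI can confound. Person-level random effects do not cure it, because they are assumed to be unrelated to the predictors.

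At stake is how far the Aim 1 slopes can be read as associations of diet and activity change with weight change, independent of starting size. A secondary question is whether adjustment would sharpen the estimates.

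**Working it through.** **1. The plan's own figure.** Inputs from the Power calculation section: R² = 0.10 from 10 predictors, alpha 0.025, power 90%, average cluster size 1.5, ICC 0.7, 20% loss, 375 planned.

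- Overall F test, f² = R²/(1 − R²), non-centrality n·f²: required n = 222, against 226 stated (1.8% apart). Power at 226 is 0.908, so the stated figure is reproduced closely.
- Design effect: 1 + (1.5 − 1) × 0.7 = 1.35, as stated; 226 × 1.35 = 305.1, matching 305.
- Effective n from 375 recruited: 375 × 0.8 / 1.35 = 222. Power there is 0.901.

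(The step from 305 to 371 for dropout is a separate matter and does not affect this point.)

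**2. Cost and precision of adding baseline BMI.** The documents do not say how much variance in weight change baseline BMI explains. Call that share c and treat it as an assumption. Then f² = 0.10/(1 − 0.10 − c), with one fewer residual degree of freedom, and the residual standard error shrinks by the factor √((0.90 − c)/0.90).

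| Assumed c | Required n | × 1.35, then / 0.8 | SE reduction | Power at effective n = 222 |
|---|---|---|---|---|
| 0 | 222 | 375 | none | 0.901 |
| 1% | 219 | 370 | 1 − √(0.89/0.90) = 0.6% | 0.905 |
| 5% | 210 | 355 | 1 − √(0.85/0.90) = 2.8% | 0.922 |
| 10% | 198 | 335 | 1 − √(0.80/0.90) = 5.7% | 0.940 |

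The extra degree of freedom costs no meaningful power even if BMI explains nothing. The gain is small across the range. It would probably be smaller still for within-person slopes, because a time-constant covariate removes mainly between-person variance.

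**3. Confounding.** With standardised variables, let g be the effect of baseline BMI on weight change and h its correlation with composition change. The bias in the unadjusted slope is g × h. Neither quantity is in the documents. A simulation with an assumed true slope of 0.20 gave:

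| g | h | g × h | Unadjusted slope | Adjusted slope |
|---|---|---|---|---|
| 0.1 | 0.1 | 0.01 | 0.21 | 0.20 |
| 0.2 | 0.2 | 0.04 | 0.24 | 0.20 |
| 0.3 | 0.3 | 0.09 | 0.29 | 0.20 |
| 0.3 | 0 | 0 | 0.20 | 0.20 |

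This simulation has one change per person, so it shows the between-person component alone. In the planned multilevel model that component is only part of the slope, so the bias would be diluted. The last row shows that BMI must relate to both changes before any bias arises.

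**The case against.** The strongest reply has four parts.

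- **The list may be open.** The covariates are introduced as ones that will be included, in a condensed article whose full analysis plan is not shown. This stands to the extent that one cannot say BMI has been ruled out. But the article does not defer the covariates; it names them aim by aim, and no body-size measure is named for a weight outcome.
- **Change on change removes most of the problem, and heavier people dieting more is not confounding.** The second half is right: a path from BMI through diet change to weight change runs through the exposure. Bias needs BMI also to affect weight change by another route. The first half is right for stable level effects only, for the reason given under the concern.
- **Adjusting a change score for its own starting value is contested in an observational cohort.** This stands. Averaging early weigh-ins reduces the shared error but does not abolish it, particularly for someone who weighs weekly and so supplies few readings. The risk is small if within-person fluctuation is small beside the spread between people, which is an assumption. Reporting both models meets it.
- **Weight-control practices, asked at each timepoint, measure intent more directly.** They do, but practices reported during the year may be part of the diet and activity change under study. Baseline BMI precedes it.

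A reader might also infer more than the documents support:

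- **That the heaviest participants dominate the fit.** If kilogram change scales with body mass, its variance relative to percent change is 1 + CV². With an assumed CV of 18% to 25%, that is 1.032 to 1.0625, a 3% to 6% difference, which does not amount to dominance.
- **That percent change is the correct outcome.** The article does define weight stability in relative terms ("whether they have been weight stable (within 5% of body weight) in the past 3 months"), but that is a baseline question and does not make kilogram change an error.
- **That Aim 3 has the same gap.** Aim 3 models children's outcomes, including an already standardised BMI z-score. Parental BMI may itself result from the family environment being studied, so adjusting for it could remove the effect sought.
- **That smoking must be added.** The article collects it, but nothing in the documents shows that its absence from the Aim 1 sentence biases the slopes.

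**Conclusion.** The point holds for Aim 1 as a modest one. The named adjustment set has no measure of starting body size, the data for one are collected, and the model as described leaves room for confounding by baseline BMI. The size of that confounding is unknown. It is the product of two relations that the documents do not quantify, from 0.01 to 0.09 on a standardised slope when both are assumed to lie between 0.1 and 0.3, and less once within-person information is mixed in. Precision is not a strong argument: standard errors fall by about 0.6% to 5.7% under an assumed 1% to 10% of variance explained, and planned power is already about 0.90.

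A reader might go further and infer a materially inflated false-positive rate. The documents do not support a figure for that, since any such rate rests wholly on assumed correlations. No number stated in the article is wrong on account of this point.

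**What to change.** In the Aim 1 analysis, add baseline BMI to the named covariates, computed from the stadiometer height and an average of early weigh-ins. State in advance which weigh-ins count. Report the activity and diet estimates with and without BMI, so that the reader can see both the confounding that adjustment removes and any sensitivity to regression to the mean. Percent or log weight change may be added as a sensitivity analysis, but the kilogram outcome need not be replaced. Aim 3 needs no change on this account.

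The cost is plan wording, one degree of freedom and one extra reported model. No new data are needed, and power is unchanged or slightly better.

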## Abstract

**Background:**

Almost one in three Australian adults are now obese, and the rate continues to rise. The causes of obesity are multifaceted and include environmental, cultural and lifestyle factors. Emerging evidence suggests there may be temporal patterns in weight gain related, for example, to season and major festivals such as Christmas, potentially due to changes in diet, daily activity patterns or both. The aim of this study is to track the annual rhythm in body weight, 24 h activity patterns, dietary patterns, and wellbeing in a cohort of Australian adults. In addition, through data linkage with a concurrent children’s cohort study, we aim to examine whether changes in children’s body mass index, activity and diet are related to those of their parents.

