**Methods:**

A community-based sample of 375 parents aged 18 to 65 years old, residing in or near Adelaide, Australia, and who have access to a Bluetooth-enabled mobile device or a computer and home internet, will be recruited. Across a full year, daily activities (minutes of moderate to vigorous physical activity, light physical activity, sedentary behaviour and sleep) will be measured using wrist-worn accelerometry (Fitbit Charge 3). Body weight will be measured daily using Fitbit wifi scales. Self-reported dietary intake (Dietary Questionnaire for Epidemiological Studies V3.2), and psychological wellbeing (WHOQOL-BREF and DASS-21) will be assessed eight times throughout the 12-month period. Annual patterns in weight will be examined using Lowess curves. Associations between changes in weight and changes in activity and diet compositions will be examined using repeated measures multi-level models. The associations between parent’s and children’s weight, activity and diet will be investigated using multi-level models.

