In sum, the evidence suggests that temporal patterning in activity and diet across the year leads to cyclical spikes in weight gain, which accrue over time. However, research to date has been piecemeal, focussed on only diet, or activity patterns or weight gain, and not all three simultaneously. Additionally, Australian data are lacking; it is possible that international findings may not reflect Australian patterns, due to key differences in timing of festivities by season (e.g. Australian Christmas falls in summer) and climate (e.g. Australian winters are relatively mild and summers relatively harsh). Finally, most research on the effects of daily physical activity, sedentary behaviour and sleep has examined the activities in isolation and applied standard multivariate statistical techniques which assume that daily activities are independent. However, activity data are naturally co-dependent – they occur in a finite 24-h window, thus if one activity increases (e.g. moderate to vigorous physical activity), then another must decrease (e.g. sleep). Research employing frequent waves of data collection, taking into account the compositional nature of activity data, is required to understand temporal patterns of weight gain, activity and dietary intake in order to enable the design and implementation of interventions at the time they are needed most. For example, if most annual weight gain occurs at Christmas, and this coincides with unhealthy eating patterns, dietary interventions could be targeted in the lead up to Christmas. This aims of this study are therefore to:
Describe the annual rhythms in adults’ body weight, daily activities and eating patterns, and determine whether changes in body weight across the year are associated with changes in activity and diet compositions.Determine whether changes in children’s body mass, activity and diet compositions are related to those of their parents, andExamine whether parental factors (parenting style and home environment) are associated with changes in children’s body mass, activity and diet compositions.

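### The child outcome of the parent-child aim has different names in different places; the Aim 2 analysis uses weight, without height, where Aim 3 uses BMI z-score for the same children

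*Protocol article*

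**What the plan says.** The protocol article names the child outcome of the parent-child aim in four places:

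- **Abstract, Background:** body mass index ("we aim to examine whether changes in children’s body mass index, activity and diet are related to those of their parents").
- **Abstract, Methods:** weight ("The associations between parent’s and children’s weight, activity and diet will be investigated using multi-level models").
- **Aims, at the end of the section on weight gain across the year:** body mass ("Determine whether changes in children’s body mass, activity and diet compositions are related to those of their parents"). The third aim in that list uses the same term for the children.
- **Statistical analysis, Aim 2:** weight ("Associations between change in children’s (dependant variables) and parents’ (independent variables) weight, activity, and diet compositions").

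The Aim 3 analysis opens with "The association between change in children’s body mass index z-score". The Statistical analysis section states that Aims 2 and 3 both draw on the Life on Holidays families, so the children are the same. The Aim 2 adjustment set is given as "Covariates will include parental and child age, sex, socioeconomic status, and child total energy intake". Child height and change in height are not listed.

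**The concern.** The dependent variable of one of the three stated aims cannot be identified with certainty from the text. An analyst who follows the Aim 2 paragraph literally would model change in kilograms. One who follows the abstract Background would model change in BMI. One who carries the Aim 3 outcome across would model change in BMI z-score. These are different outcomes in children who are still growing.

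The literal reading is also the least suitable of the options that the document itself names. The study is about obesity, and the Discussion would use parent-child concordance to support family-based intervention. A child's weight rises with height even when weight status does not change. A model of weight change without height therefore mixes growth with the change that the aim is about. Aims 2 and 3 would also report different child outcomes for the same children, with no reason given.

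**Working it through.** No stated figure in the protocol rests on this point, so there is nothing to reproduce. The check is a comparison of the text, followed by an illustration.

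**1. Is it one construct or several?** In the list of aims, the second and third aims describe the child outcomes in identical terms. In the Statistical analysis section, that single construct becomes weight under Aim 2 and BMI z-score under Aim 3. No sentence says that weight under Aim 2 stands for BMI or BMI z-score, and none explains why the two analyses should differ. The abstract does not settle it, because its Background and Methods paragraphs disagree with each other.

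**2. Do the Aim 2 covariates deal with growth?** Child age and sex are included. They can absorb part of the average growth trend, meaning the mean gain expected at a given age and sex. They cannot absorb the difference between two children of the same age and sex who grow by different amounts, because neither height nor height change is in the model.

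**3. Illustration of what remains.** All inputs here are assumptions, because the document gives no child heights, growth rates or BMI values: height H from 1.15 to 1.45 m, growth g from 0.04 to 0.07 m a year, BMI B from 15 to 20 kg/m². For a child whose BMI does not change,

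weight gain = B × ((H + g)² − H²).

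- Lowest: 15 × (1.19² − 1.15²) = 15 × 0.0936 = 1.40 kg a year.
- Highest: 20 × (1.52² − 1.45²) = 20 × 0.2079 = 4.16 kg a year.

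For two children with the same height (1.30 m) and the same constant BMI (17 kg/m²):

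- Growth of 4 cm: 17 × (1.34² − 1.30²) = 17 × 0.1056 = 1.80 kg.
- Growth of 7 cm: 17 × (1.37² − 1.30²) = 17 × 0.1869 = 3.18 kg.
- Difference: 3.18 − 1.80 = 1.38 kg.

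Neither child's BMI has changed, yet their values on the outcome differ by about 1.4 kg, and age and sex would not explain that difference if they share both. Constant BMI is used only to keep the arithmetic simple. It is not the same as constant BMI z-score, because the reference for the z-score changes with age.

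**4. Are the data for the alternative already required?** Yes. Change in BMI z-score under Aim 3 needs the children's weight, height, age and sex at the relevant assessments, for the same children.

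**The case against.** The strongest reply is that weight in the Aim 2 sentence is shorthand. The sentence compresses parents and children into one list, the abstract Background says body mass index for the same aim, and Aim 3 specifies BMI z-score. The children's measurements also belong to the separate Life on Holidays protocol, which is not shown and may fix the scaling. This has force: the document does not establish that unscaled kilograms will be analysed, and a reader should not infer that it does. It does not remove the inconsistency, since the article states the dependent variable and does so in conflicting ways.

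Three stronger readings are tempting and are not supported:

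- **Growth swamps the parental signal.** A reader might set the assumed 1.4 to 4.2 kg a year beside the roughly 0.5 kg a year that the article cites for adults (1.4/0.5 = 2.8; 4.2/0.5 = 8.4) and conclude that the Aim 2 estimate is mostly noise or is biased. A ratio of mean gains shows neither. That would depend on variances and covariances, which the document does not give, and the age and sex covariates already remove part of the mean trend. The 0.5 kg is also a net yearly figure, while the article cites 0.4 to 0.9 kg for the US holiday season alone.
- **Shared family body size creates a false association.** This is possible in principle, but nothing in the document allows it to be sized, and the point does not depend on it.
- **The parental measure must be rescaled too.** Parental height is measured once, at baseline, so change in parental BMI is weight change divided by a constant for each parent. Keeping weight for parents is not an error.

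Different child outcomes under Aims 2 and 3 would also not be wrong in themselves if they were intended and explained.

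**Conclusion.** The point stands as an inconsistency in the identity of the Aim 2 child outcome, with a consequence for the analysis if the Aim 2 paragraph is followed literally. In that case, differences between children in height growth stay in the dependent variable, and it does not isolate change in weight status. This conclusion rests on the wording of the article and on the children still growing. The only child age range given, 5 to 12 years, belongs to the general-advertising recruitment route; for Life on Holidays the article says only that the children came from schools.

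The size and direction of any effect on the Aim 2 estimate cannot be derived from the document. The kilogram figures above only illustrate that the growth component is not negligible under the assumed values. Aim 1 and the power calculation, which addresses Aim 1, are untouched.

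**What to change.** In the Aim 2 paragraph of the Statistical analysis section, name change in the child's BMI z-score as the dependent variable for weight status, beside the activity and diet compositions. Use that same name in the Background and Methods paragraphs of the abstract and in the list of aims. Parental weight change may stay as the exposure. If change in the child's weight is in fact intended for Aim 2, say so and state how height growth is handled.

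The cost is a change of wording before analysis. The child data are already needed for Aim 3, so no new measurement is required, and the sample size does not change.
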